## Abstract

**Background:**

Extraction of lower first permanent molars in children is common. There is uncertainty among clinicians as to whether a ‘compensating extraction’ (removal of the upper first permanent molar to prevent it over erupting) is necessary despite current guidelines recommending this. As a result, unnecessary dental extractions may be carried out or children may be failing to receive extractions required to achieve optimal long-term oral health. In addition, the decision to extract fewer or more teeth affects management options (local anesthetic injections alone, inhalation sedation or general anesthesia) needed to support the child with the surgical procedure(s).

The SIXES (Should I eXtract Every Six) dental trial investigates clinical effectiveness and quality of life for conventional treatment (following the guideline of compensation extraction of the upper first permanent molar) compared with the alternative intervention (removal of lower first permanent molars but no extraction of the upper).

**Methods/Design:**

This is a multicenter, two-arm parallel group randomized clinical trial. Allocation will be web-based randomization. Practitioners in primary and secondary care settings, reflecting the points of presentation and treatment of eligible patients, will recruit 400 children, aged 7 to 11 years requiring extraction of lower first permanent molars but who have upper first permanent molars of good prognosis. Baseline measures (prior to treatment) and outcome data (at one and five years, or when the patient reaches 14 years of age) will be assessed through study models and child/parent questionnaires.

The primary outcome measure is degree of tipping of the lower second permanent molar, (favorable outcome is tipping less than 15°).

The secondary outcomes are type of anesthetic/sedation used, residual spacing (between lower second premolar and second permanent molar), orthodontic treatment requirement, quality of life, and over-eruption in the intervention group. Assessors will be blinded where possible.

**Discussion:**

SIXES dental trial investigates whether compensating extraction of upper first permanent molars should be carried out following loss of lower first permanent molars. Currently dentists and orthodontists face a dilemma in clinical decision-making, relying on the lowest level of evidence - expert opinion. SIXES will provide evidence to support decision-making and inform practices and may result in reduced tooth extractions.

**Trial registration:**

Clinical Trials.gov Identifier: NCT01591265

## Background

### Introduction

The first permanent molars (FPMs) are the permanent teeth most commonly assessed as having a poor prognosis due to them being the permanent teeth most susceptible to dental caries in childhood [1,2] and the high prevalence of molar-incisor hypomineralization (MIH) [3,4]. It is accepted that while forced extraction of FPMs is rarely ideal, with appropriate timing and case selection, it can result in an acceptable occlusion for the child [5,6]. Preferably, all cases where planned loss of FPMs is anticipated should be managed jointly with an orthodontist, but this is not always possible. Treatment planning is complicated by the need to consider other factors alongside occlusal aspects such as the possible absence of other permanent teeth, the prognosis of the remaining molars, the anticipated cooperation of the child with any proposed restorative treatment, and socioeconomic factors. In addition, FPM teeth are the largest in the dentition, and their successful extraction places demands on both the child and the clinician.

To assist dentists in treatment planning, a national guidance document is available [7]. As well as advice on timing of extractions, this guidance recommends that in Class I and Class II cases, the extraction of a mandibular FPM should be compensated by the extraction of the opposing maxillary FPM. The rationale for compensating the extraction of a lower FPM is that an unopposed maxillary FPM may over-erupt and prevent mesial migration of the erupting lower second permanent molar. However, it has been suggested that there is little evidence to support this being a significant risk [8]. Furthermore, the extraction of an additional FPM places an increased burden on both the child and the dental team providing care for them, and may tip the balance of decision as to whether the extractions can be carried out under local anesthesia, towards favoring dental general anesthesia [9].

In summary, current clinical guidelines state that when a lower FPM is extracted, the upper FPM should also be extracted, yet this recommendation is based on little or no evidence. This randomized clinical trial will provide the evidence to answer this question: Is it necessary to extract the upper FPM routinely when extracting the lower FPM in the mixed dentition in order to prevent over-eruption of the upper FPM, which can cause occlusal problems?

Should this study find the procedure to be unnecessary, it will result in a reduction in the number of teeth extracted. The impact of the study would then be significant for children and their carers, as well as providers and purchasers of dental treatment.

### Rationale for the study

#### Do unopposed molar teeth over erupt?

There is good evidence that unopposed permanent molar teeth can over erupt. Kiliaridis [10] reported on 84 permanent molar teeth, which were known to have been unopposed for a minimum of 10 years, in 53 adults (mean age 65, range 40 to 89). While 18% of the molars showed no over-eruption (to visual examination of study models), 58% had over-erupted by up to 2 mm, while 24% had over-erupted in excess of 2 mm. There was no difference detected between maxillary and mandibular molars.

One cross-sectional study of 100 adults [11] with unopposed molar teeth, and a matched control group of 100 adults with opposing molars, reported over-eruption in 92% of unopposed molar cases. There was a mean value of 1.44 mm more over-eruption in the unopposed molar group than in the control group with opposing molars. This was less than 2 mm in 73% of cases. The extent of over-eruption was significantly greater in maxillary unopposed teeth than in mandibular unopposed teeth.

In a study of 91 adults who had molars which had been either partially or completely unopposed for a minimum of five years [12] partial occlusal contact did not inhibit overeruption but did increase the likelihood of tipping. Smith [13] looked at overeruption of lower second permanent molars in 42 patients following loss of maxillary second molars, comparing them with 42 matched control patients. Overeruption of the unopposed mandibular second molars was found to occur, but this was largely confined to the distal aspect (which was unopposed by the maxillary FPM), with a mean value of less than 1mm. Christou [14] and Compagnon [15] both reported overeruption of unopposed posterior teeth over time but, again, these studies involved adults.

#### Is potential overeruption of a maxillary first permanent molar a significant risk to the development of a healthy occlusion?

For patients within the age range for consideration for planned loss of FPMs, there are two possible complications of over-eruption of an unopposed maxillary FPM: 1) prevention of desired mesial movement of the mandibular second permanent molar and 2) the development of occlusal interferences, leading to temporo-mandibular joint dysfunction syndrome (TMDS).

#### Prevention of mesial movement of mandibular second molar

The Royal College of Surgeons of England (RCS) national guidance document [7] cites Holm [16] as the main data source for supporting compensating extractions following loss of lower FPMs. This paper is a conference report, reviewing 1,119 cases involving loss of one or more FPMs over a 10-year period at the Hamburg Public Orthodontic Institute. The review was carried out principally to assess the proportion of cases involving loss of FPMs, and the patterns of extraction. Although the poorest outcomes were found in cases of uncompensated extraction of lower FPMs, no data were presented to support this. In contrast, Mejare [8] reviewed 32 patients (mean age 18 years) who had loss of one or more FPMs in childhood (mean age 10 years) due to molar incisor hypomineralization (MIH). Of this sample, five patients had an uncompensated extraction of a lower FPM, and in none of these patients was over-eruption of the upper FPM noted. In addition, in a longitudinal study of 27 children who had one or more FPMs extracted due to MIH, Jalevick [17] reported no significant occlusal problems with the four children with uncompensated extractions of lower FPMs, and recommended against the need for compensating extractions. Patient satisfaction was also investigated in this study, and it was reported that of the five children assessed as having need of orthodontic correction of their occlusion, three of them declined treatment as they felt there was no need for it.

#### Development of occlusal interferences

Craddock, [18] in a cross-sectional study of 100 adult patients with at least one unopposed posterior tooth, and 100 control subjects, reported that 53% of the patients in the unopposed molar group had retruded contact position contacts or excursive interferences, compared with 12% of the controls. However, Agerberg [19] reported in a study of 140 teenagers and young adults that 89% of all subjects showed at least one occlusal interference, and that no correlation between the number of missing teeth and the number of interferences could be found. Heikinheimo [20], in a longitudinal study of 167 adolescents, found that none had a functionally optimal occlusion at 15 years of age, and that although around 30% of the sample had some tenderness to palpation of the muscles of mastication, none was found to have significant symptoms of TMDS.

## Trial Purpose

The purpose of this trial is to provide reliable evidence for clinicians as to whether compensating extraction of upper FPMs (as per current guidelines) should be carried out following loss of lower FPMs.

## Trial Objectives

The objective of this trial is to determine whether compensating extraction of upper FPMs following loss of lower FPMs in children is of benefit. The particular benefits being investigated are related to the resulting occlusion and oral health-related quality of life.

## Methods/Design

### Overview

The SIXES Trial is a multicenter, two-arm parallel group randomized controlled trial using a superiority framework (see Figures 1 and 2). Measurements will be taken at one year after treatment and then again at either five years after treatment or when the patient reaches 14 years of age, whichever occurs first. The trial will be set in both primary and secondary care settings, reflecting the points of presentation and treatment of eligible patients. Figure 1 shows details of screening, recruitment, randomization and participant follow-up schedule and Figure 2 is a trial CONSORT type flow diagram [21] with projected numbers of participants throughout the trial.

**Figure 1 F1:**
[figure not shown]
Screening, recruitment, randomization and participant follow-up schedule of the SIXES Trial.

**Figure 2 F2:**
[figure not shown]
**SIXES trial flow diagram.** CONSORT [21] flow chart with projected numbers of participants throughout trial.

### Basis for the study design

This study will recruit patients from both secondary and primary care settings and include general dental practitioners, pediatric dentists and orthodontists in order to attract a representative sample of patients (by wide net). This study design is based around routine care as practitioners use both the current guidelines and the proposed intervention in their treatment of patients. It aims to assess these practices relative to one another and, as such is a low-risk study assessing current practice.

Study recruitment is taking place over a 24-month period commencing in July 2012, with the coordinating site being the Dundee Dental Hospital Orthodontic and Paediatric Dentistry Departments. Other sites will be recruited to the trial.

Dentists are considered eligible to participate if they treat child patients and are willing to undergo good clinical practice (GCP)/research governance framework (RGF) training. Tailored training relevant to dental studies involving children for study GCP and RGF is being delivered by Tayside medical Science Centre (TASC).

Prior to study recruitment at any individual site, there will be a site initiation visit and site staff will receive training on the study design, methodology, clinical intervention and on maintaining trial documentation, including the CRFs, questionnaires and investigator site file.

### Participant inclusion criteria

Age: 7 to 11 years

Dental History: Able to cooperate with dental treatment Regular attender or considered likely to return for follow-up

Social History: Child and carer able to understand study documentation and give consent to participate in study

Dental condition: One or two lower FPMs requiring extraction Upper FPMs are sound or restorable/restored with good long term prognosis (that is, has or requires a single surface restoration with caries less than half-way into dentine, restoration with a simple restoration)Confirmed presence of all second premolars and all second molars

### Participant exclusion criteria

Medical history: Medical contraindication to dental extractions

Dental condition: Poor prognosis of premolars or permanent second molar teethAll four upper incisors in crossbite Poor prognosis of upper FPM Confirmed absence of one or more second premolars and second molarsDeclines to have impressions taken.

### Interventions

The patient will continue to have all other treatment planned and carried out as normal. The only difference in treatment will be related to the FPM extractions (one side only per patient will be entered into the trial). For patients allocated to the control arm, both the upper FPM and lower FPM will be extracted. For patients in the intervention arm, only the lower FPM will be extracted.

Only one side of the mouth will have data collected for the study. For patients who require extraction of lower FPMs on both sides of the mouth, the decision of which side to include in the study will be taken through randomization.

The control group will have the normal standard intervention according to the current standard guidelines, and will receive routine patient care with the normal practice of compensation extraction, while the intervention group will have removal of their lower FPMs but no compensation extraction of the upper FPM will be carried out.

### Training in intervention

As the proposed intervention is removing a tooth, which is standard clinical practice, no specific training on that procedure is required.

### Participant timeline

Patients will be identified by clinicians participating in the trial from either the patients’ own dentist or orthodontist; or a secondary care orthodontic or pediatric department.

Patients who are found, during routine dental examination or assessment, to require extraction of a lower FPM will be assessed by their dentist or orthodontist for meeting the inclusion criteria. Patients who meet the inclusion criteria will have the study discussed with them and their parents/guardians by their clinician. A participant information leaflet will be given. Patients will be given a further appointment for the extractions, at least 24 hours after receiving the information and at this time, the study will be discussed again. However if treatment is to be carried out at the same appointment (for example, where patients are in pain), there will be time allowed for the patient and parent/carer to read the documentation and ask any questions to ensure they have sufficient time and information for consent to be informed. Consent/assent processes will be carried out and then randomization undertaken. Extraction(s) will be carried out as per randomization and the remaining treatment plan.

The patient will complete the first questionnaire and have upper and lower impressions taken for study models to be cast. When the patient returns for 1-year follow-up, they will complete the Year 1 Follow-up Questionnaire and have upper and lower impressions taken for study models to be cast. When the patient returns for final follow-up (at five years or when the patient has reached 14 years of age), they will complete the Final Follow-up Questionnaire and have upper and lower impressions taken for study models to be cast.

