### Participant recruitment and retention

Patients who meet the inclusion criteria will receive an invitation to take part in the trial will be identified during attendance at appointments with clinicians participating in the trial.

It is anticipated that the majority of patients will be attending for a six monthly routine check-up appointment (primary care GDP or community dentist) or a non-urgent secondary care assessment (practice-based specialist orthodontist, hospital-based orthodontic service and pediatric department).

Patients attending for routine check-up appointments or non-urgent assessments, who meet the inclusion criteria, will be assessed by the dentist for eligibility, and asked whether they wish to participate when they return for treatment at their next appointment. The patients and parents will be given information on the study to take home with them. Consent will be taken at the subsequent appointment by a dentist participating in the trial as a principal investigator (PI). Randomization will be carried out prior to this appointment and treatment.

For children who attend for urgent appointments, presenting in pain, the patients and their parents will also be approached at the time of their appointment about whether they wish to participate in the study. Because there is the need to alleviate the child’s symptoms as soon as possible, usually involving extraction of the tooth, there is no scope for 24 hours to reflect on the trial information. For this reason some patients will be invited to participate at their assessment appointment. Consent and randomization will still follow best practice, and parents and patients will still be given time to look at the patient information sheets and consider the study. The intervention in this study (extraction of a single tooth compared with extraction of two teeth) still allows the patient to return for conventional treatment (extraction of the upper FPM) should they be allocated to the intervention arm but change their mind about participation at a later date.

On enrollment to the SIXES trial, parents and patients will be given ‘calling cards’ saying that they are participating in the study, with details of their dentists and who to contact regarding the study.

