**Other clinical records**			
Dental impressions and occlusal registration	**X**	**X**	**X**

At time of extraction (T0):

1. Dental impressions and a record of occlusal registration will be taken for study models

2. The dentists will complete a case report form (CRF) (patient details, which arm randomized to, which side treatment was allocated to, what kind of anesthetic was used - local anesthesia (LA)/inhalation sedation (IHS)/general anesthesia (GA)/other type of sedation)

3. Children’s Oral Health-Related Quality of Life (OHRQoL) questionnaire

4. Parental OHRQoL questionnaire

After 1 year (T1):

1. Dental impressions and a record of occlusal registration will be taken for study models

2. Record of any dental treatment (to remaining upper FPMs) or orthodontic treatment provided since initial intervention

3. Children’s OHRQoL questionnaire

4. Parental OHRQoL questionnaire

After 5 years or when child turns 14 (whichever is first) (T2):

1. Dental impressions and a record of occlusal registration will be taken for study models

2. Dentists will record any dental treatment (to remaining upper FPMs) or orthodontic treatment provided since initial intervention

3. Children’s OHRQoL questionnaire

4. Parental OHRQoL questionnaire

The CRFs and questionnaires will all be marked with the patient’s unique study ID number which will be linked to the enrollment log for the trial.

Study models will be 3D scanned to measure occlusal changes. All patients’ lower study models will be assessed with regard to the tipping of the lower second permanent molar relative to the occlusal plane. The scanning software will be able to create an occlusal plane from cusp tips in order to calculate the degree of molar tipping. Not all patients will have an erupted lower second permanent molar at the earlier time points in the study.

Only the groups of patients who do not have the upper FPMs extracted will require their upper study models to be assessed for FPM over-eruption. Each patient’s upper models will be superimposed on the palatal rugae and any movement in the *x, y* and *z* plane of the upper FPMs will be recorded.

In addition, the 3D scans of the models will be used to give ABO occlusal index scores and to assess and measure any residual spacing between the lower second permanent molar and the lower second premolar.

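### Statements on when T0 is measured conflict: as written it falls after unblinded randomization, and possibly after extraction

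*Protocol article*

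**What the plan says.** Four places in the protocol article bear on when T0 is measured.

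- **Abstract, Methods/Design:** "Baseline measures (prior to treatment) and outcome data". This is the only explicit statement that T0 precedes treatment.
- **Participant timeline:** "Consent/assent processes will be carried out and then randomization undertaken", followed by "Extraction(s) will be carried out as per randomization and the remaining treatment plan". The next paragraph opens with "The patient will complete the first questionnaire and have upper and lower impressions taken for study models to be cast" and goes on to the one-year and final visits.
- **Data collection, T0 list after Table 1:** the list is headed "At time of extraction (T0" and contains impressions, the CRF and both quality-of-life questionnaires. The CRF records "which arm randomized to, which side treatment was allocated to, what kind of anesthetic was used".
- **Participant recruitment and retention,** on children seen at routine or non-urgent visits who return for consent and treatment: "Randomization will be carried out prior to this appointment and treatment".

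Table 1 has a single baseline column. It lists randomization above the CRF, the questionnaires and the impressions, and gives no order within the visit. The Blinding section says that neither children nor carers can be blinded once the group is allocated.

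**The concern.** A baseline measure is useful because allocation cannot have influenced it. If child and parent answer the T0 questionnaires knowing the arm, that protection is lost. If they answer after the extractions, the score also carries the short-term effect of treatment, and the two arms have had different treatment: on the study side, two teeth are removed in the control arm and one in the intervention arm.

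The protocol itself gives reasons to expect such an effect. Table 2 lists pain and swelling as common after extraction, and nausea and drowsiness as common after general anesthesia. The Background says that the extra extraction may shift the choice towards general anesthesia.

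A T0 difference between arms could then be read neither as chance imbalance nor as treatment effect. Up to 40 sites are expected. Some could follow the Abstract and others the timeline, and the article mentions no record of the order by which to separate them at analysis.

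**Working it through.** No formula tests this point, so the check sets the statements side by side.

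**1. T0 relative to randomization.** The Participant timeline mentions T0 data after randomization. Participant recruitment and retention puts randomization before the treatment appointment for routine attenders, while the Data collection section ties T0 to the extraction. Taken together, T0 follows randomization. The Abstract does not contradict this, because it promises measurement before treatment and is silent on randomization. No statement provides for T0 before allocation. So T0 after unblinded allocation is well supported by the text.

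**2. T0 relative to extraction.**
- Abstract: before.
- Participant timeline: mentioned after, in a new paragraph, with no word such as then or after.
- T0 list: at extraction, side not stated. The CRF in that list can be completed only once treatment has been given, but this does not date the questionnaires or impressions.
- Table 1: baseline column, no order within the visit.

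The order in the timeline and the Abstract cannot both be followed, and the T0 list does not decide between them.

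**3. Which data are exposed.**
- *Child and parent quality of life.* Both are to be compared between groups at each time point, T0 included. Data management and statistical methods also enters the scores at the three time points into a Friedman test. A T0 score taken after extraction would change the reference point of that test in both arms, and by an amount that may differ between them.
- *ABO scores.* The endnotes take secondary outcomes 1 to 3 from models that include baseline. If impressions follow extraction, control-arm models lack the upper first molar and intervention-arm models have it, so baseline occlusion differs by construction.
- *Over-eruption.* Upper models are superimposed only for patients who keep the upper first molar, so its absence in control models does not enter.
- *Residual space.* This is a lower-arch measure, and the lower first molar is removed in both arms. Late impressions would not create the same built-in difference.
- *Primary outcome.* Tipping is judged at final follow-up, and the article notes that the tooth concerned may not have erupted at the earlier visits. It is little affected.

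**4. Size.** Let D be the true between-arm difference at a later visit and d the between-arm difference in T0 that allocation has caused. A direct comparison at the later visit estimates D and does not use T0. A comparison of change from T0 estimates D − d, so the whole of d enters. The article only says that analysis between time points will be considered, and it gives nothing from which to set d. No number can be attached.

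**The case against.** The strongest case against has four parts.

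- **Sequence is inferred from sentence position.** The timeline uses a sequencing word only between consent and randomization. The sentence on the first questionnaire opens a paragraph that may simply list the three data-collection occasions, and the one explicit statement, in the Abstract, says before treatment. This stands in part. A reader might infer that T0 is in fact a post-treatment measure; the document does not establish that. It establishes conflicting statements, one of which would have that result if followed.
- **The order may be given elsewhere.** Figure 1 is not shown, and a full protocol may set out the steps of the visit. That limits certainty about what sites will do. It does not remove the conflict, because the article does state an order and its statements disagree.
- **Measurement after allocation but before extraction contradicts nothing in the Abstract.** This is correct, and it is why the two timings are kept apart above. Self-reported T0 scores given with the arm known are still a weakness.
- **The harm depends on analyses that are not fixed.** This largely stands. A reader might go on to claim that a set fraction of any T0 shift passes into an adjusted treatment effect. No baseline-adjusted model is specified, so no such fraction can be stated. What remains is the between-group comparison at T0 and the Friedman test, both of which the article does plan.

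**Conclusion.** The statements on T0 timing conflict and should be reconciled. As written, T0 falls after unblinded allocation. If the Participant timeline is followed in the order given, T0 also falls after extraction, and the T0 quality-of-life scores and T0 models could then be affected by arm. The exposure is to secondary outcomes, chiefly child and parent quality of life and, for the models, the ABO score. Between-group comparisons at one year and at final follow-up do not use T0, and the primary outcome is little affected.

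The size is not quantifiable from the document. It depends on how many participants have T0 taken late and on how far knowledge of the arm or the extractions moves the answers; neither is given. The conclusion assumes that sites work from the order in this text, with Figure 1 and the full protocol unseen.

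**What to change.** Reconcile the Abstract, Participant timeline, Participant recruitment and retention, and Data collection to one explicit order: consent/assent, T0 questionnaires and impressions, randomization, extraction. Record the date and time of each step on the CRF. Leave the CRF items on arm and anesthetic for completion after treatment, and say so, so that they are not read as dating the questionnaires.

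Flag any T0 data obtained after randomization or after extraction, and do not treat them as baseline in any change-from-T0 or across-time analysis.

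**Cost.** The edits are to wording and to CRF time fields; no procedure is added. The one practical burden falls on routine attenders: consent and T0 must be completed before randomization, which the recruitment section now places ahead of the appointment. Moving it would also settle a related conflict, since that section takes consent at the appointment and so puts randomization before consent, while the Participant timeline puts consent first. Pre-treatment data that were not collected at the time cannot be recovered later.
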